### Statistical analysis

#### Data set population determination

In this research, the Intention to treat (ITT) and Per-Protocol set (PPS) will be used together. In line with the selection and exclusion criteria in the program, good compliance, no other related treatment will be carried out during the research, and the case report forms (CRF) table will be completed, which has an evaluable curative effect index. The patients with poor curative effect will be also included in the PPS set as ineffective cases. For missing data, we will use LOCF method to make up. We will use the Statistical Package for Social Sciences (SPSS-IBM^®^,Armonk, NY: IBM Corp.) version 20 for Windows to complete statistical analysis of this study.

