### Inclusion criteria

People will be eligible for inclusion if they meet the following criteria: (1) First ever unilateral ischemic stroke diagnosed by imaging and the course of the disease ranged from 2 weeks to 6 months. (2) UL dysfunction as indicated by the Fugl-Meyer motor function score ≥20-40/66. (3) Aged 40–70 years, regardless of sex. (4) No severe cognitive or communication impairment as indicated by the Mini-mental state examination (MMSE) ≥ 24 points.

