### Sample size calculation

The main purpose of the experiment is to compare whether the curative effect of the experimental group is better than that of the control group. The main evaluation index of curative effect will be the change of upper limb Fugl-Meyer scale. The calculation of the sample size will be based on data from previous research and our previous experiment (18). As the study involves two groups, the sample size calculation formula for a two-sample mean comparison is as follows:

(1)
$$\begin{array}{l} n_{c}=\frac{{\left(z_{1-\alpha }+z_{1-\beta }\right)}^{2}\sigma^{2}\left(1+\frac{1}{K}\right)}{{\left(\mu_{T}-\mu_{C}-\Delta \right)}^{2}} \end{array}$$

where, Z_1_-α = 1.960, Z_1_-β = 0.842, σ = 2.0 (standard deviation), K = 1(ratio of participants in the experimental and control groups), 1 = 3 (optimality bounds), α = 0.025 (2.5% one-tailed significance level), and β = 0.20 (80% power), μ_T_ = 6.6 (predicted mean in experimental group); μ_C_ = 2.3 (predicted mean in control group). The calculated required sample size is 38 participants for each group. Assuming the dropout rate is 20%, 45 participants per group (total of 90 participants) need to be recruited.

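### Last observation carried forward is the only stated method for missing data in patients expected to keep gaining, so the primary contrast is biased; power is lost only if the 3-point bound is tested

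*Protocol article*

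**What the plan says.** Under Data set population determination, the protocol article gives one rule for missing values: "For missing data, we will use LOCF method to make up". The rule is tied to no outcome, visit or reason for missingness. The same paragraph says that "the Intention to treat (ITT) and Per-Protocol set (PPS) will be used together". Case distribution analysis adds a comparison of dropout and elimination rates between groups.

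Patients qualify if "the course of the disease ranged from 2 weeks to 6 months" (Inclusion criteria). Under Sample size calculation, "The main evaluation index of curative effect will be the change of upper limb Fugl-Meyer scale". The planning values there are "μ_T_ = 6.6 (predicted mean in experimental group"), "μ_C_ = 2.3 (predicted mean in control group") and "σ = 2.0 (standard deviation"), with a bound of 3 points, one-sided alpha 0.025 and 80% power. On losses: "Assuming the dropout rate is 20%, 45 participants per group (total of 90 participants) need to be recruited".

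Fugl-Meyer-UE is scheduled at baseline, 2 and 4 weeks after the start of treatment, and 4 weeks after its end (Outcome measures, Table 1). Efficacy analysis describes a between-group t-test, or a rank sum test, and does not mention the bound.

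**The concern.** Carrying the last score forward is unbiased only if a patient's score would have stayed flat after the last visit attended. The plan expects the opposite: both arms gain, and the experimental arm gains almost three times as much (6.6 / 2.3 = 2.9). A frozen baseline or week-2 score therefore understates the final score, and by more points in the arm that is expected to gain more. This holds even when dropout is unrelated to outcome.

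At stake are the size of the primary estimate and, if dropout differs between arms, the false-positive rate. If the trial has to show a difference above 3 points, its power is also at stake, because only 4.3 - 3 = 1.3 points of the expected effect lie above that bound.

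**Working it through.** **Reproducing the plan's sample size.** Inputs from Sample size calculation: difference 6.6 - 2.3 = 4.3, bound 3, SD 2.0, z-values 1.960 and 0.842, ratio 1.

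n = (1.960 + 0.842)² × 2.0² × 2 / (4.3 - 3)² = 7.851 × 8 / 1.69 = 37.17, rounded up to 38. This matches the stated 38 per group, so the trial is sized against the 3-point bound.

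**Assumptions for the rest.** Let f be the share of the final gain already reached at the last visit attended, the same in both arms. The document does not give f, so a range is shown. Dropouts' carried change has mean f × μ and SD 2√f. There are 45 patients per arm, and all dropout comes before the primary visit.

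**Equal dropout of 20% in both arms.** Each arm mean becomes 0.8μ + 0.2fμ, so the contrast is 4.3 × [1 - 0.2(1 - f)]. Each arm's variance is that of the mixture: 0.8(2² + μ²) + 0.2(4f + f²μ²) - (arm mean)². Power against the bound is Φ[(contrast - 3)/SE - 1.96].

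Example with f = 0.5:
- Means: 0.8 × 6.6 + 0.2 × 3.3 = 5.94 and 0.8 × 2.3 + 0.2 × 1.15 = 2.07; contrast 3.87.
- SDs: 2.311 and 1.952; SE = √[(2.311² + 1.952²)/45] = 0.451.
- Power: Φ(0.87/0.451 - 1.96) = Φ(-0.03) = 49%.

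| f | Contrast | Excess over 3 | Power against 3 |
|---|---|---|---|
| 0 (baseline carried) | 3.44 | 0.44 | 12% |
| 0.25 | 3.66 | 0.66 | 26% |
| 0.5 | 3.87 | 0.87 | 49% |
| 0.75 | 4.09 | 1.09 | 73% |

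Simulated t-tests (40,000 runs) gave 13% for f = 0 and 48% for f = 0.5.

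**Comparator.** An unbiased analysis with 45 × 0.8 = 36 completers per arm has SE = 2√(2/36) = 0.471. Power is Φ(1.3/0.471 - 1.96) = 79%.

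**The same test against zero.** In the worst row, SE is 0.562 and 3.44/0.562 = 6.1, so power exceeds 99%.

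**Dropout in one arm only (20%, baseline carried).**
- Control loses patients: 6.6 - 0.8 × 2.3 = 6.6 - 1.84 = 4.76, above the true 4.3.
- Experimental arm loses patients: 0.8 × 6.6 - 2.3 = 5.28 - 2.3 = 2.98, just under the bound.

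**False positives.** Assume that both arms truly gain 4.3, that dropout is 10% experimental and 30% control, and that the test is against zero.
- f = 0: false difference (0.9 - 0.7) × 4.3 = 0.86; SDs 2.294 and 2.585; SE 0.515; one-sided type I error Φ(0.86/0.515 - 1.96) = 39%.
- f = 0.5: false difference (0.95 - 0.85) × 4.3 = 0.43; SDs 2.053 and 2.091; SE 0.437; type I error about 17%.

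The nominal level is 2.5%. With equal dropout under the same null, it stays at 2.5%.

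**The case against.** The strongest objection concerns power. A reader might infer that carrying scores forward removes much of the trial's power whatever test is run. The documents do not support that. The only efficacy test described has no bound, and against zero the planned effect is so large relative to the SD that power stays above 99%. The loss exists only if the bound in the sample size section is actually tested. This objection stands.

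A reader might also infer that the direction of bias is unpredictable even under completely random dropout. It is not. With equal random loss the contrast is always pulled below 4.3 on the plan's means. Bias in either direction needs different loss in the two arms, and the plan gives one overall rate of 20%. Unequal loss is plausible, since one arm has 30 extra minutes of hands-on treatment per session, but it is an assumption.

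The timing of dropout is not stated either. The case f = 0 requires every dropout to leave before the week-2 visit. If half of the dropouts are lost only after a week-4 primary visit and the rest carry half their gain, the contrast is 4.3 × (1 - 0.1 × 0.5) = 4.09 and power against the bound about 69%. If only the follow-up score is missing and week 4 is carried, the harm is probably small.

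Finally, the plan has a per-protocol analysis and compares dropout rates. The first is a companion analysis largely of completers, and the second would reveal unequal loss. Neither corrects the intention-to-treat estimate, and the plan attaches no change of analysis to what they show.

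**Conclusion.** The concern holds as a bias in the primary analysis. The article commits to the method outright, so this is not a detail left to a fuller plan, and the plan's own predicted gains contradict the flat course that the method assumes. Equal random dropout of 20% shrinks the expected contrast from 4.3 to between 3.44 and 4.09 for f from 0 to 0.75. One-sided loss of 20% with baseline carried moves it to 4.76 or 2.98. Under the assumed null with 10% versus 30% dropout, one-sided type I error is about 17% to 39%.

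The power loss is conditional: 12% to 73% over the same range of f, against 79%, and only if the 3-point bound is tested and all dropout precedes the primary visit. The value of f, the timing of dropout and any imbalance between arms are assumptions. The method should be changed before unblinded analysis, because under plausible dropout it can alter the primary conclusion.

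**What to change.** Replace carrying forward for Fugl-Meyer-UE with a method valid under missing at random. One suitable choice is a likelihood-based repeated-measures mixed model on all observed visits, with baseline score, visit, group and group-by-visit; multiple imputation would also serve. Report the contrast at whichever time point the plan names as primary. Add a sensitivity analysis for informative dropout, for example control-based imputation, and keep last observation carried forward at most as a further sensitivity analysis. The sample size and efficacy sections should also be reconciled on whether the 3-point bound is tested, since the power consequence depends on it.

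The cost is revised wording in the analysis section and a little more programming. The visits are already scheduled, so no new data are needed.

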### Statistical analysis plan

#### Case distribution analysis

The shedding and elimination cases will be described, and the drop rate and elimination rate of the two groups will be compared.

#### Comparability analysis

According to the analysis of the basic situation of the two groups before treatment, the sex of the patient will be divided into two variables, and the chi-square test of two independent sample rates will be used. W-test and F-test will be used to determine that the continuous variables such as Fugl-Meyer-UE, MS, MBI and MEP and fNIRS measurements (Lateral Index, RSFC values, zfALFF values) in the baseline is in accordance with normal distribution and homogeneity of variance, and two independent sample *t*-tests will be used for comparison. If these data do not conform to normal distribution or homogeneity of variance, Wilcoxon rank sum test will be used to compare the measurement data. If the comparison of the variables in the baseline between the two groups is statistically significant and professional, the variable will be analyzed as a covariable multiple efficacy index.

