### Randomization and blinding

A simple randomization method will be used in this experiment. Individuals recruited in the experiment will be divided into two groups. Ninety random numbers will be generated by Excel and the random distribution table will be determined by sorting method. In this study, the envelope random allocation method will be used to put the cards printed with the allocation group into sequentially coded, opaque and sealed envelopes one by one according to the random distribution sequence. When the researchers determined that the subjects are qualified, a researcher who did not participate in the treatment, evaluation and statistics opened the envelopes sequentially and assigned the subjects to an appropriate group. An experienced blinded therapist will perform the assessment, he/she is one of the clinical therapists in the hospital. Emergency unblinding will be performed if a serious adverse event occurs. In the event of unblinding during the study, the involved subject will be removed from the study protocol. After trial completion, participant grouping will be revealed, and data analysis will commence. The research data will be properly preserved by specialized researcher. The blind data and the database will be submitted to experimental statistics professionals for statistical analysis and statistical analysis report will be written. After the statistical report is completed, the principal researcher will write a summary report of the research.

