#### Efficacy analysis

The data in accordance with normal distribution and homogeneity of variance in the main and secondary indicators will be compared with *t*-test to see if the difference between the two groups before and after treatment is statistically significant. The rank data with non-normal distribution or uneven variance will be analyzed by Wilcoxon rank sum test.

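### The primary FMA-UE analysis is chosen by baseline and assumption tests: it usually omits baseline FMA-UE, and it treats Wilcoxon as a remedy for unequal variances

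*Protocol article*

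**What the plan says.** Three sections of the protocol article bear on this point.

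- **Sample size calculation.** The main index is the change in FMA-UE. The trial is sized on a difference in mean change (6.6 against 2.3, common SD 2.0) that must exceed a bound of 3.
- **Comparability analysis.** Baseline variables, FMA-UE among them, are compared between groups by t-test or Wilcoxon, as a W-test and an F-test decide. A variable becomes a covariate only if the comparison "is statistically significant and professional, the variable will be analyzed as a covariable multiple efficacy index".
- **Efficacy analysis.** Main and secondary indicators that are normal with homogeneous variance go to a t-test. The next sentence reads: "The rank data with non-normal distribution or uneven variance will be analyzed by Wilcoxon rank sum test".

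No baseline-adjusted model is fixed for the primary outcome, and no unequal-variance t-test is named. Table 1 schedules FMA-UE at baseline.

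**The concern.** These are stated rules, so the objection is to the rules and not to detail left for a later document.

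First, baseline FMA-UE is the obvious prognostic covariate and is already collected, yet it enters only after a significance test. Under randomisation that test can be significant only by chance. The further requirement of professional relevance is undefined and leaves room for judgement.

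Second, the t-test/Wilcoxon switch means that neither the hypothesis tested nor the effect measure is known in advance. A rank-sum test gives no mean difference to set against the 3-point bound, and it does not repair unequal variances.

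At stake are precision in a small trial and a primary result that may not address the hypothesis used for sizing.

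**Working it through.** **Inputs from Sample size calculation:** one-sided α 0.025 (z = 1.960), power 80% (z = 0.842), σ = 2.0, means 6.6 and 2.3, bound 3, ratio 1:1, 38 per group, 20% dropout, 45 recruited per group.

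**Assumed, because the article does not give them:** 5% level for the baseline and assumption tests; baseline-change correlation r from 0.17 to 0.5 in absolute value; SD ratio between arms 1 to 3; normal or gamma (shape 2) data.

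**1. The plan's own figure.** The excess over the bound is 6.6 − 2.3 − 3 = 1.3.

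n = (1.960 + 0.842)² × 2.0² × 2 / 1.3² = 37.17, rounded up to 38. This reproduces.

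**2. How often the covariate enters.** A 5% test on a randomised baseline is significant in about 5% of trials (simulated 4.9-5.2%). Baseline FMA-UE is therefore left out in about 95%, before the professional criterion is applied.

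**3. Cost in precision.** With 36 completers per group (45 × 0.8), residual SD = 2.0 × √(1 − r²), SE = residual SD × √(2/36) and power = Φ(1.3/SE − 1.960).

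| r | 1 − r² | SE | Power |
|---|---|---|---|
| 0 (unadjusted) | 1 | 0.471 | 78.7% |
| 0.17 | 0.971 | 0.465 | 79.9% |
| 0.3 | 0.910 | 0.450 | 82.4% |
| 0.5 | 0.750 | 0.408 | 89.0% |

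The lower end is derived as follows. If baseline FMA-UE is uniform over the 20-40 entry window, its SD is 20/√12 = 5.77. If the post-treatment SD is the same, then 2.0² = 2 × 5.77² × (1 − ρ). This gives a baseline-post correlation ρ = 0.94 and r = √((1 − 0.94)/2) = 0.17.

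Simulated SE at 45 per group, for unadjusted, gated and ANCOVA:
- r = 0.17: 0.422, 0.421, 0.418
- r = 0.3: 0.421, 0.416, 0.405
- r = 0.5: 0.422, 0.408, 0.368

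The gated rule recovers little of the available gain.

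**4. Type I error of the covariate gate.** On the change score, for ρ from 0.3 to 0.9, it is 0.042 to 0.050 at a nominal two-sided 0.05. It is slightly conservative, not inflated.

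**5. The test switch.** With normal data and equal variances, the pretests still send about 15% of trials to Wilcoxon (three tests at 5%: 1 − 0.95³ = 14.3%).

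Rejection rate with equal true means, 45 per group, nominal two-sided 5%:

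| Data | SD ratio | Wilcoxon |
|---|---|---|
| Normal | 1.5 | 5.0-5.5% |
| Normal | 2 | 5.8% |
| Normal | 3 | 6.7-7.0% |
| Gamma, shape 2 | 1.5 | 11.4-11.7% |
| Gamma, shape 2 | 2 | 18.3-18.9% |
| Gamma, shape 2 | 3 | 27.2-27.8% |

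Ranges are across repeated simulations. Welch stayed between about 4.8% and 5.9% in these scenarios. The full pretest-then-test rule gave nearly the same rates as Wilcoxon alone: 5.0-7.1% with normal data and 11.4-27.3% with gamma data.

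**The case against.** **The precision gain may be trivial.** At r = 0.17 ANCOVA cuts variance by only 3% and power moves from 78.7% to 80%. A larger gain needs a post-treatment spread that differs from the baseline spread, which the article does not say. This stands, so the gain is given as a range that starts there.

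**Wilcoxon may not reach FMA-UE.** The Efficacy analysis sentence opens by referring to rank data, which could mean ordinal scales only. But its triggers mirror the t-test condition for the main and secondary indicators. On the narrow reading, a non-normal or heteroscedastic primary outcome would have no test at all. The broader reading is more likely, not certain.

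**Stronger readings that the article does not support:**

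- *The Wilcoxon analysis is simply invalid.* If treatment has no effect and the two distributions are identical, its error rate is correct. With symmetric data in equal arms the departure is mild. The article plans one common SD and gives no sign of strong skew, so the large rates are scenarios.
- *Uncorrected baseline imbalance biases the result badly.* The change score already subtracts baseline. Even an imbalance just short of significance (1.987 × 5.77 × √(2/45) = 2.4 points) shifts the contrast by only r × 2.0/5.77 times that: about 0.15 points at r = 0.17 and 0.42 at r = 0.5, against a planned difference of 4.3.
- *These choices are made with groups known.* Randomization and blinding says "After trial completion, participant grouping will be revealed, and data analysis will commence", but the same section also says that blinded data go to the statisticians. Blinding at analysis is ambiguous. The t-test/Wilcoxon switch is in any case rule-driven; only the professional criterion leaves discretion.

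**Conclusion.** The point holds as a matter of poorly chosen stated rules. The primary analysis depends on the data and usually omits baseline FMA-UE.

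The covariate gate does no harm to type I error. Its cost is the power forgone, from about 1 percentage point (r = 0.17) to about 10 (r = 0.5) at 36 completers per group. This assumes that σ = 2.0 is the SD of change and that the 20% dropout occurs.

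The variance switch has a different fault: Wilcoxon does not address a mean difference above 3. Its error rate for equal means is close to nominal with symmetric data. It is materially wrong only if unequal spread and skew occur together, which is an assumption and not something the article reports.

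**What to change.** - Prespecify one primary analysis of FMA-UE change: ANCOVA on group and baseline FMA-UE, with unequal-variance (robust) standard errors and a 95% CI for the mean difference. Use it whatever the baseline comparisons or assumption tests show.
- Drop the significance-and-professional gate and the normality/variance pretest switch for the primary outcome.
- Keep Wilcoxon as a sensitivity analysis, and for ordinal scales such as the Modified Ashworth.
- Make the baseline comparisons descriptive.

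The cost is minor analysis wording. The baseline measurement is already scheduled, and nothing changes in conduct or recruitment.

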#### rTMS

rTMS intervention will be performed using a transcranial magnetic stimulator (MagTD; Wuhan Yiruide Medical Equipment New Technology Co., Ltd., Wuhan, China) and a figure of eight coil (YRD, maximum magnetic field intensity = 2T, diameter = 9 cm, Wuhan Yiruide Medical Equipment New Technology Co., Ltd.). First, the resting motion threshold (RMT) of rTMS will be determined. The surface recording electrode will be placed at the abdomen of the abductor pollicis brevis muscle on the affected side (if MEP is not detected, the unaffected side will be used) of the UL, the reference electrode will be placed at the tendon, and the ground wire will be connected to the wrist. Adjust the central position of the magnetic stimulation coil to the best position of motor evoked potential (MEP) of abductor pollicis brevis, and gradually reduce the stimulation. In the resting state, at least 5 of the ten stimuli with a minimum magnetic stimulation intensity of >50 μV MEP amplitude will be considered RMT on the side of the cerebral cortex. During the treatment, the patient will be in the supine position, and the motor area of the ipsilesional side of the brain (M1) will be used as the stimulation target. The “8” coil is tangent to the surface of the skull, the midpoint will be aimed at the stimulation target, the stimulation intensity is 100% RMT, the stimulation frequency is 10 Hz, each sequence is 20 pulses, the sequence interval is 8s, with a total of 1200 pulses in 10 min. The patients will be treated 5 times a week for 4 weeks.

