### Outcome measures

The assessment will be conducted on four time points, including at baseline, 2 weeks and 4 weeks after the beginning of the treatment, and 4 weeks after the end of the treatment (Table 1). All assessments will be performed by therapists who do not know the specific group.

**Table 1 T1:** SPIRIT figure.

	**Screening**	**Baseline**	**Intervention**			**Follow weeks**
Time Point	**-t** _ **2** _	**-t** _ **1** _	**0**	**w2**	**w4**	**4w**
Enrollment						
Informed consent	**√**					
Demographic information	**√**					
Medical history	**√**					
MMSE	**√**					
Eligibility assessment	**√**					
Random allocation		**√**				
Interventions						
Tui Na+TMS group						
Cnventional group						
Assessments						
Fugl-Meyer-UE		**√**		**√**	**√**	**√**
MS		**√**		**√**	**√**	**√**
MAS		**√**		**√**	**√**	**√**
MBI		**√**		**√**	**√**	**√**
MEP		**√**		**√**	**√**	**√**
fNIRS		**√**		**√**	**√**	**√**
Adverse event			**√**	**√**	**√**	**√**

Description of the protocol. -t2, first contact with participants; -t1, baseline evaluation;0, starting day of the treatment; w2, 2weeks after the start of treatment;w4, 4 weeks after the start of treatment and post evaluation;4w, 4 weeks after the end of treatment; MMSE, Mini-Mental State Examination; Fugl-Meyer-UE, Fugl-Meyer Upper Extremity Scale; MS, Muscle Strength; MAS, Modified Ashworth, MBI, Modified Barthel Index; MEP, Motor evoked potentials; fNIRS, functional near-infrared spectroscopy; The orange line represents the treatment time in the figure, with a total of 4 weeks of treatment.

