#### Motor evoked potentials

MEP is the muscle motor potential recorded by stimulating the motor cortex in the target muscle, and to examine the overall synchronization and integrity of the motor nerve transmission from the cortex to the muscle and the conduction pathway. TMS results in sequential activation of upper motor neurons, which in turn leads to spinal cord motor neuron activation, and is recorded by the surface Electromyography in the target muscle (32). In this research, at least 5 out of 10 monopulse stimuli will be given to the cortical representative region (M1) of the contralateral abductor pollicis brevis to induce MEP with an amplitude >50 μV as the motor threshold. The resting motor threshold (RMT) will be analyzed.

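### Baseline variables become covariates only after a significant baseline test; fixing baseline FMA-UE as a covariate in advance costs almost nothing and probably gains a little precision

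*Protocol article*

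**What the plan says.** Comparability analysis tests the two arms against each other at baseline: chi-square for sex, and a t-test or Wilcoxon rank sum test for "the continuous variables such as Fugl-Meyer-UE, MS, MBI and MEP and fNIRS measurements". A variable enters the efficacy analysis as a covariate only if its baseline difference "is statistically significant and professional, the variable will be analyzed as a covariable multiple efficacy index". I read the second condition as clinical judgement of relevance.

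Efficacy analysis gives the default. Data that meet the normality and equal-variance conditions go to a t-test "to see if the difference between the two groups before and after treatment is statistically significant", and other data to a Wilcoxon rank sum test. Neither test has a covariate, and no covariate is named in advance.

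Three other statements bear on this:
- Sample size calculation: "The main evaluation index of curative effect will be the change of upper limb Fugl-Meyer scale".
- Randomization and blinding: "A simple randomization method will be used in this experiment", with allocation in sequentially coded, opaque, sealed envelopes and no stratification mentioned.
- Outcome measures: "The assessment will be conducted on four time points, including at baseline". Table 1 marks FMA-UE at baseline.

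**The concern.** With concealed random allocation, any baseline difference between the arms is due to chance. Whether adjusting for a variable sharpens the treatment comparison depends on how strongly it predicts the outcome, and a baseline p-value does not measure that. The rule therefore selects covariates on the wrong criterion. It will usually leave out a prognostic variable, and it will sometimes include a useless one because of a chance imbalance.

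Two things are at stake. The model for the primary outcome is settled only after the baseline data have been inspected, partly by a judgement with no stated criterion. And whatever precision baseline FMA-UE could add to the FMA-UE comparison is almost entirely given up.

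**Working it through.** **Inputs from Sample size calculation.** SD of change 2.0; expected means 6.6 and 2.3; margin 3; one-sided alpha 0.025 (z = 1.960); 80% power (z = 0.842); 38 per arm before dropout and 45 recruited. From Inclusion criteria: baseline FMA-UE between 20 and 40.

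**The plan's own figure.** Effective gap = 6.6 − 2.3 − 3 = 1.3.
n = (1.960 + 0.842)² × 2.0² × 2 / 1.3² = 37.17, rounded up to 38. This matches.

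**Unadjusted precision.** SE = 2.0 × √(2/n). Power against the margin = Φ(1.3/SE − 1.96).
- 38 per arm: SE 0.459, power 80.9%.
- 45 per arm: SE 0.422, power 86.9%.

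**How often the rule adjusts.** About 5% of randomised trials for any one variable, and less often once the judgement condition is applied.

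**What a fixed baseline covariate gives.** With r the correlation of baseline FMA-UE with its change, SE is multiplied by √(1 − r²). The documents do not give r, so a range is needed.

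One value follows from the plan's figures under two assumptions. If baseline FMA-UE is uniform on 20 to 40, its SD is 20/√12 = 5.77. If variances are equal before and after treatment, 2.0² = 2 × 5.77² × (1 − ρ), so the pre-post correlation ρ is 0.94. Then r = −(1 − 0.94) × 5.77/2.0 = −0.17 and r² = 0.03.

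| Absolute r (assumed) | r² | SE cut | 95% CI half-width, 38 / 45 per arm | Power against margin, 38 / 45 per arm |
|---|---|---|---|---|
| 0 | 0 | 0% | 0.90 / 0.83 | 80.9% / 86.9% |
| 0.17 | 0.03 | 1.5% | 0.89 / 0.81 | 82.0% / 87.9% |
| 0.3 | 0.09 | 5% | 0.86 / 0.79 | 84.4% / 89.8% |
| 0.5 | 0.25 | 13% | 0.78 / 0.72 | 90.5% / 94.5% |

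The table ignores the cost of estimating the covariate's slope. For one covariate, the expected variance inflation is (N − 3)/(N − 4), which is 87/86 at N = 90. Break-even is therefore r² = 1 − 86/87 = 0.011. At r² = 0.03 the net SE cut is 1 − √(0.97 × 87/86) = 0.9%.

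**Simulation.** 45 per arm, SD 2.0, gap 1.3, one-sided 2.5%, 10,000 trials per setting. The rule is applied to baseline FMA-UE alone, without the judgement condition.

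| r | No adjustment | Rule | ANCOVA on baseline FMA-UE |
|---|---|---|---|
| 0 | 86.5% | 86.4% | 86.2% |
| 0.3 | 86.1% | 86.3% | 88.8% |
| 0.5 | 86.5% | 87.4% | 93.8% |

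The trigger fired in 4.4% to 5.5% of trials. Type I error was 2.2% to 2.9% for every analysis (Monte Carlo SE 0.16 points). A separate run at r = −0.17 (20,000 trials) gave 86.3% unadjusted and 86.8% with ANCOVA at 45 per arm, and 80.4% and 80.8% at 38 per arm.

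**Against zero.** At the planned difference of 4.3, power = Φ(4.3/0.459 − 1.96), above 99.9% even at 38 per arm without adjustment.

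**The case against.** The strongest reply is that little is lost. The main index is a change score, so baseline is already subtracted, and only a remaining correlation between baseline and change can be exploited. On the plan's SD and eligibility range, with equal variances, that correlation is about −0.17 and the simulated gain is about half a point of power. Moreover, Efficacy analysis names no margin. If the t-test is against zero, power is above 99.9% whatever is done. All of this stands, and it limits the point to a small gain. It does not defend the rule, which does not select on prognostic value.

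Three stronger readings are tempting, but the documents do not support them.

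- **Bias or false positives.** A reader might infer that a data-dependent covariate choice biases the comparison or inflates type I error. Allocation is random and concealed, and simulated type I error stayed near 2.5%.
- **MEP status as a second fixed covariate.** The rTMS section foresees patients without a response, with recording "on the affected side (if MEP is not detected, the unaffected side will be used) of the UL", while the Motor evoked potentials section says "The resting motor threshold (RMT) will be analyzed". A test on the threshold therefore does not test presence or absence of the response. But the documents give neither the share of such patients nor any effect on FMA-UE gain, so a required MEP covariate would rest on assumption alone.
- **A trigger in a third of trials.** Counting eight independent baseline variables gives 1 − 0.95⁸ = 34%. The list of continuous variables is open-ended, the variables may be correlated, and the judgement condition reduces the rate. Only the rate of about 5% per variable is firm.

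**Conclusion.** The point holds as a modest design improvement, to be considered rather than required. The protocol states a rule that picks covariates by a baseline p-value. This leaves the primary model dependent on the data and recovers almost none of the precision that baseline FMA-UE might offer: at r = 0.5, 0.9 points of power against 7.3 for ANCOVA.

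The likely size is small: an SE cut of about 1.5% (0.9% net) under the equal-variance assumption, and 5% to 13% only if the correlation is 0.3 to 0.5. The power figures apply only if the 3-point margin is tested. The validity of the comparison is not in question.

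**What to change.** Replace the significance trigger with one sentence: the primary FMA-UE change is analysed by ANCOVA with treatment arm and baseline FMA-UE as fixed terms, whatever the baseline comparisons show. Report baseline comparisons descriptively. State in the same place what becomes of the Wilcoxon fallback, for example as a sensitivity analysis. Do not require MEP status as a covariate.

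No new measurement, visit or patient is needed, because FMA-UE is already assessed at baseline. The cost is one degree of freedom and, if baseline is not prognostic, well under one point of power (86.5% to 86.2% in the simulation).
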